### Biomechanical assessment

Plantar pressure is recorded using the Pedar-X system (Novel, Munich, Germany) at 100 Hz. The patient walks barefoot on a 10 m flat walkway at a self-selected cadence (controlled between subject's trials within 96-116 steps/min), with the insole placed and fixed, using an anti-skid sock and a stripe at the ankle. Four valid trials are recorded, and we discard the first and last steps from the analysis. The foot is divided into six areas (heel, midfoot, lateral forefoot, middle forefoot, medial forefoot, hallux, and toes), using the same software for data acquisition. A time-series analysis will be performed to compare the pressure curve in each area, over the stance duration, intending to describe changes in plantar pressure distribution. Values of contact area and peak pressure will be compared in these six areas.

Kinematic gait parameters are acquired using three-dimensional displacement of passive reflective markers (20 mm in diameter) tracked with six infrared cameras (OptiTrack FLEX: V100, Natural Point, Corvallis, OR, USA) (Trombini-Souza et al., 2011). The markers are placed on the subject using a standard Cleveland Clinic marker set (iliac spine antero-superior, superior aspect of the greater trochanter, lateral knee joint line, lateral malleolus, calcaneus, and head of the fifth metatarsal) [70]. Extra markers are placed bilaterally at the medial knee joint line, medial malleolus, and first metatarsal joint for the static standing trial, in order to determine relative joint centres of rotation for the knee, ankle, and longitudinal axis of the foot. These extra markers are removed in the gait trial. In addition, three non-collinear reflective markers are fixed at two squares, forming sets of technique cluster. One of these is placed in the lateral thigh and the other over the shank. Theses landmarks are determined by the same physiotherapist who performs the blind assessment. The laboratory coordinate system is established at one corner of the force plate, and all initial calculations are based on this coordinate system. Each lower limb segment (foot, shank, and thigh), based on surface markers, is modelled as a rigid body with a local coordinate system that coincides with the anatomical axes, and translations and rotations of each segment are reported relative to neutral positions defined during the initial standing static trial.

Ground reaction forces are acquired by a force plate (AMTI OR-6-1000, Watertown, MA, USA) embedded in the centre of the walkway.

Force and kinematic data acquisition are synchronized and sampled by an A/D card (AMTI, DT 3002, 12 bits) at 100 Hz. Mathematical analysis of the kinematic data will be performed using Visual3D software (C-motion, Kingston, ON, Canada), and the ground reaction force analysis will be performed using a custom-written Matlab function (MathWorks, Natick, MA, USA). The variables to be analysed are: (1) joint angles and (2) net ankle moments in the sagittal and frontal planes; and (3) step length and (4) duration. These variables will contribute to discussion of the possible changes in plantar pressure distribution, especially the ankle position in the initial and terminal stance phases.

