**Discussion:**

Herein, we present a more comprehensive and specific physiotherapy approach for foot and ankle function, by choosing simple tasks, focusing on recovering range of motion, strength, and functionality of the joints most impaired by diabetic polyneuropathy. In addition, this intervention aims to transfer these peripheral gains to the functional and more complex task of foot rollover during gait, in order to reduce risk of ulceration. If it shows any benefit, this protocol can be used in clinical practice and can be indicated as complementary treatment for this disease.

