### Sample size and statistical analysis

The sample size calculation was made using an effect size of 0.36 (moderate effect size), considering the primary outcome measure of peak plantar pressure. We took the SD estimates from a study we completed, wherein we recruited a similar patient cohort [71]. A sample size of 46 subjects is needed to provide 81% power to detect a moderate effect difference between the highest and lowest group pressure means, assuming an alpha level of 0.05 and an statistical design of F test of repeated measures (between and within effects), and assuming a 10% loss to follow-up. The statistical analysis will be based on intention-to-treat analysis, and general linear models of analysis of variance for repeated measure will be used to detect treatment-time interactions. The outcome measures will be compared among baseline, 12 weeks, and 24 weeks. Cross-correlation analysis will also be provided between primary and secondary variables if it shows any relevance.

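### The trial is sized on one peak-pressure test, but peak pressure is compared in six foot areas (seven are listed) and no primary area or summary is named

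*Protocol article*

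**What the plan says.** All references are to the Protocol article.

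- **Biomechanical assessment** defines the regions: "The foot is divided into six areas (heel, midfoot, lateral forefoot, middle forefoot, medial forefoot, hallux, and toes". The stated count is six; the list has seven entries.
- The same section plans two kinds of comparison in every region. One is of curves: "A time-series analysis will be performed to compare the pressure curve in each area, over the stance duration". The other is of single values: "Values of contact area and peak pressure will be compared in these six areas".
- **Outcome measures** names foot rollover, described by time-series analysis of plantar pressure distribution, as the main outcome. It names no area and no summary value. Contact area is in neither the main nor the secondary list.
- **Sample size and statistical analysis** works from one effect size: "using an effect size of 0.36 (moderate effect size), considering the primary outcome measure of peak plantar pressure". The test is set by "assuming an alpha level of 0.05 and an statistical design of F test of repeated measures (between and within effects", and the result is "A sample size of 46 subjects is needed to provide 81% power", allowing for 10% loss. The planned model is repeated-measures analysis of variance for treatment-time interactions over baseline, 12 and 24 weeks. Area does not appear in it.
- The main **Discussion** cites lower plantar pressures and larger contact areas as examples of recovery.

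**The concern.** The number of areas is contradictory within one section, so a reader cannot tell whether hallux and toes are one region or two. That choice affects what is measured and could be made after the data are seen.

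The primary outcome is also not pinned down. The sample size treats peak plantar pressure as one variable with one effect size and one alpha, while the measurement section yields that variable six or seven times per patient. Nothing says which of these carries the conclusion. Contact area adds to the uncertainty, because it is compared in every region and cited as a sign of recovery without being listed as an outcome.

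At stake is the meaning of a positive result. With no designated quantity, a single significant area could be presented as the primary finding, and the false-positive rate of that practice would exceed the 5% on which the sample size was calculated.

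**Working it through.** **Inputs from the article.** Areas: 6 (stated) or 7 (listed). Alpha 0.05, effect size f = 0.36, N = 46, power 81%, loss 10%, three assessments, two groups.

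**Assumed, not in the article.** The correlation between area-level tests (0 to 0.95 shown), separate testing of each area, and no adjustment.

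**1. The plan's own figure.** After 10% loss, 46 × 0.9 = 41.4, so about 41 or 42 patients are analysed. For a group-by-time F test with 2 groups and 3 times, the numerator has 2 degrees of freedom and the error has 2(N − 2). Take noncentrality λ = f² × error df, with f² = 0.1296:

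| N analysed | Error df | λ | Power at 0.05 |
|---|---|---|---|
| 41 | 78 | 10.11 | 80.4% |
| 42 | 80 | 10.37 | 81.5% |

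This reproduces the stated 81%, as one test on one variable. Other conventions do so less well or not at all: a between-groups F test at an assumed correlation of 0.5 gives 78.6-79.6%, a single-time-point test 61-62%, and the interaction test with a correlation-scaled noncentrality more than 94%.

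**2. Chance of at least one false positive for peak pressure over k areas.** For independent tests it is 1 − 0.95^k:

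- k = 6: 1 − 0.7351 = 26.5%
- k = 7: 1 − 0.6983 = 30.2%

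Simulated two-sided tests with equal correlation ρ give:

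| ρ | 6 areas | 7 areas |
|---|---|---|
| 0 | 26.5% | 30.2% |
| 0.5 | 20.7% | 22.9% |
| 0.8 | 13.9% | 14.9% |
| 0.95 | 8.9% | 9.3% |

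**3. Favourable direction only.** If only a fall in pressure would be called success, each test contributes about 0.025. For independent tests, 1 − 0.975^6 = 14.1% and 1 − 0.975^7 = 16.2%. Positive correlation would lower these. Halving alpha is an approximation, because the planned interaction test has two degrees of freedom and no single direction.

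**4. Cost of adjusting instead of choosing.** Bonferroni over seven areas uses 0.05/7 = 0.00714. On the variant in step 1, power in a given area falls to 54.0% (N = 41) or 55.6% (N = 42). Holding 81% would need 63 analysed, or 63/0.9 = 70 recruited. Over six areas (0.00833), power is 56.1% or 57.7%, with 61 analysed and 68 recruited. Holm is never less powerful than Bonferroni, so these are lower bounds for Holm.

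**The case against.** The strongest reply is that the inflated error rate depends on an analysis that the article never states. Alpha 0.05 appears once, as a sample-size input. The text says values will be compared, not that each area is tested at 0.05. Area could enter the model as a within-subject factor, and a multiplicity rule could sit in a full protocol or analysis plan that is not shown. This stands: the absence of an adjustment rule is not the fault here, and the percentages are conditional. It does not remove the contradictory count or the undesignated primary quantity. Both lie in what the article itself fixes, and which quantity is primary is a protocol matter.

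Two stronger readings are tempting.

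- A reader might infer from the abstract that any significant area counts as success: "If it shows any benefit, this protocol can be used in clinical practice". That is a closing remark about possible clinical use. It names no test, threshold or area, so it is not a decision rule.
- A reader might count contact area as well and reach 12 or 14 tests, with 46% (1 − 0.95^12) or 51% (1 − 0.95^14) for independent tests. Contact area is not a listed outcome, those figures count unfavourable results too, and independence is unlikely for regions of the same foot in the same steps. Nor does the 24-week visit clearly add tests, since one treatment-time test spans all three assessments.

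A further objection is that reducing foot rollover to one area loses the stated idea of pressure distribution over the whole foot. That has force, and it is why a summary value or an adjusted set of areas should remain open as alternatives.

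**Conclusion.** The point holds in a limited form. Two defects are certain from the text: six areas are announced and seven listed, and the single primary outcome used for the sample size corresponds to no named area or summary. The unlisted status of contact area is a third, smaller inconsistency.

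The false-positive risk is conditional on separate unadjusted tests of peak pressure and on reading any one significant area as success. Under those conditions it is roughly three to six times the nominal 5% for correlations from 0.8 down to 0, and still about 9% at 0.95. It is about three times nominal for independent tests if only favourable results count. The correlation is not given in the article, so the range matters more than any one value. The power figures rest on the F-test variant that best matches the stated 81%; the article does not say which variant was used.

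**What to change.** Before the data are analysed:

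1. **Designate one primary peak-pressure quantity** for the planned treatment-time test at 0.05, and base the main conclusion on it. It can be one named area, or one summary such as the peak over the three forefoot areas. The latter fits the Background, which singles out the forefoot when linking plantar pressure to ulceration. State also that the effect size of 0.36 and the standard deviation behind it apply to the quantity chosen.
2. **Or keep all areas primary** with Holm adjustment, and restate the power or the sample size using the figures above.
3. **List the remaining areas, the pressure curves and contact area as secondary**, so that Outcome measures and Biomechanical assessment agree.
4. **Correct the count to seven, or merge hallux and toes**, and use the same number throughout.

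The first option keeps the planned sample size and power and needs no new measurement, since the areas are defined in software from the insole recording. Recruitment has begun, so the choice should be a dated amendment made before any comparison by group. The price is that a significant result in a non-primary area alone no longer supports the main conclusion, and that a single quantity describes foot rollover less fully than the whole distribution.

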### Outcome measures

The main outcome measure is foot rollover, which will be described by time-series analysis of plantar pressure distribution during gait. This variable was chosen because it reflects the alterations of kinematics, kinetics, and muscle function in the dynamic task of gait.

The secondary outcomes are foot and ankle kinetics and kinematics during gait, neuropathy signs and symptoms, foot and ankle ROM, function and muscle strength, and Activities-Specific Balance Confidence Scale [67].

### Intervention rationale

This intervention protocol is based on evidence that shows that:

(1) Foot rigidity is associated with increasing local loads and predisposes to plantar ulceration [12,20,40]. The increase in ROM of these segments could contribute to restoring foot rollover during gait.

(2) The weakness of the intrinsic foot muscles and ankle flexors and extensors represents an independent risk factor for the development of plantar ulcers, leading to a less effective plantar load distribution [14,45,47]. The strengthening and recovery of their function also could be reflected in foot rollover during gait.

(3) There is evidence that shows that patients with DPN can improve gait and confidence, suggesting a possible recovery of motor control functions at some level [58-60]. A more comprehensive exercise therapy should integrate the peripheral gains (increase in ROM and muscle function and strength) into motor tasks, such as gait. It could be achieved when requiring these gains during the execution of walking skills and simple balance exercises.

(4) The patients should perform the exercises independently at home, and the exercises should be simple enough to allow that.

The complete description of the intervention can be found in Additional file 1: Table S1.

We divided the therapeutic sessions into four blocks of exercises, characterised by the main objective of each exercise group. They are: (a) gain of foot and ankle ROM, (b) foot and ankle muscle strengthening, (c) foot and ankle functional exercises, and (d) walking skills and foot rollover training. Each session is composed of some of the exercises from the four groups. Gradual and progressive difficulty is offered to the patient, respecting any limitation due to pain and/or decrease in performance during execution. In addition, in each session, the exercises are performed following an order that starts with the passive exercises, progresses to active, and finishes with walking and functional skills. Therefore, we can promote the motor integration of peripheral gains into functional movements in every session. Although this intervention is focused only on foot and ankle exercises, we have a complete approach to the rehabilitation process that depends on the association between the afferent and efferent peripheral system and the central system to perform tasks of daily living, such as walking. Previous studies do not accomplish that specificity of selecting the segments most impaired by DPN to recover, nor do they integrate the musculoskeletal gains in the foot rollover process during gait.

During all exercises, the physiotherapist focuses on proper alignment of the segments, especially if the patient has difficulty in maintaining it, in a way that no movement compensations are allowed. During weight-bearing exercises, additional care is taken to maintain proper foot support: the toes should always touch the floor, avoiding hammering or clawing when possible, and the ankle should not be laterally tilted (with lateral deviations). Thus, self-perception of the foot and ankle position is stimulated even during the most challenging tasks.

The discontinuation criteria for the exercises during one session are cramps, moderate to intense pain, fatigue, dizziness, fear, or any other condition that exposes the patient to any kind of risk or discomfort.

### Sample size and statistical analysis

The sample size calculation was made using an effect size of 0.36 (moderate effect size), considering the primary outcome measure of peak plantar pressure. We took the SD estimates from a study we completed, wherein we recruited a similar patient cohort [71]. A sample size of 46 subjects is needed to provide 81% power to detect a moderate effect difference between the highest and lowest group pressure means, assuming an alpha level of 0.05 and an statistical design of F test of repeated measures (between and within effects), and assuming a 10% loss to follow-up. The statistical analysis will be based on intention-to-treat analysis, and general linear models of analysis of variance for repeated measure will be used to detect treatment-time interactions. The outcome measures will be compared among baseline, 12 weeks, and 24 weeks. Cross-correlation analysis will also be provided between primary and secondary variables if it shows any relevance.

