**Figure 1 F1:**
[figure not shown]
**Flowchart of the protocol steps**.

The patients allocated to the intervention group receive the treatment for 12 weeks, twice a week, 40-60 min per session. They are assessed at baseline condition (A1), after 12 weeks (A2-intervention period), and after 24 weeks (A3-follow-up period).

The patients allocated to the control group represent the crossover arm of the study. They also are assessed at baseline condition (A1) and after 12 weeks (A2). During this period, they continue to receive the usual recommended medical care at the hospital, which includes pharmacological treatment and self-care instructions. After the end of the second evaluation, they receive physiotherapy intervention for 12 weeks and are then assessed after intervention (A2'-24 weeks after baseline) and after the follow-up period (A3'-36 weeks after baseline). This design was chosen in order to increase the number of patients receiving the intervention, as we can expect losses to the follow-up evaluation due to the longer period of time required to complete all the protocol procedures (intervention and follow-up period).

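### The named repeated-measures ANOVA by default drops any patient with a missing visit, which does not fit the stated intention-to-treat principle given the 10% loss the protocol expects

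*Protocol article*

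**What the plan says.** The section on sample size and statistical analysis sets the principle and the model in one sentence: "The statistical analysis will be based on intention-to-treat analysis, and general linear models of analysis of variance for repeated measure will be used" to test treatment-time interactions. The next sentence fixes the visits: "The outcome measures will be compared among baseline, 12 weeks, and 24 weeks". The same section gives the planned size, "A sample size of 46 subjects is needed to provide 81% power", and includes the allowance "assuming a 10% loss to follow-up".

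The overview of the research design, in the text below Figure 1, explains why controls cross over to treatment: "we can expect losses to the follow-up evaluation due to the longer period of time required". It also fixes what each visit means. The intervention arm is treated from baseline to week 12 and then followed without treatment to week 24. Controls have usual care to week 12, physiotherapy from week 12 to week 24, and a follow-up visit at week 36.

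The article names no imputation, no mixed model and no other rule for a randomised patient who lacks a visit. Nor does it say that such a patient is left out.

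**The concern.** An intention-to-treat analysis keeps every randomised patient in the assigned arm. The usual general linear model procedure for repeated measures takes one complete set of visits per patient and deletes the patient if any visit is missing. Once losses occur, and the protocol expects them, the two halves of the sentence pull in different directions.

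Two things are at stake. The first is waste: a patient measured at baseline and week 12 who misses week 24 is removed altogether, including the 12-week value. Week 12 is the only post-baseline visit that compares treated with untreated patients, so this value matters most.

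The second is possible bias. Deletion makes the 12-week comparison conditional on attending a later visit that means different things in the two arms. For the intervention arm it comes 12 weeks after treatment stopped; for controls it closes their own course of treatment. Reasons for staying away could differ by arm, and the remaining completers would then no longer be the groups that were randomised.

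**Working it through.** **Inputs.** From the section on sample size and statistical analysis: N = 46, power 81%, effect size 0.36, alpha 0.05, repeated-measures F test, 10% loss, three visits. From the overview of the research design: two arms. Assumed because not stated: 1:1 allocation, and 0.36 read as Cohen's f.

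**1. Reproducing the planned size.** Of the conventions tried, the closest match is the within-between interaction with noncentrality λ = f²(N − 2)(m − 1), m = 3 visits, and degrees of freedom 2 and 2(N − 2); f² = 0.36² = 0.1296.

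| N | λ | Power |
|---|---|---|
| 41 | 0.1296 × 39 × 2 = 10.11 | 80.4% |
| 42 | 0.1296 × 40 × 2 = 10.37 | 81.5% |
| 46 | 0.1296 × 44 × 2 = 11.40 | 85.3% |

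Inflating for loss: 41 / 0.90 = 45.6, rounded up to 46. The stated 46 at 81% is thus close to 41 to 42 evaluable patients. On this reading the sample size counts a lost patient as contributing nothing, which is how a complete-case analysis behaves. The match depends on an effect-size convention that the article does not name, so it supports the point without proving it.

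**2. Patients left after default deletion.** Analysed = 46 × (1 − loss).

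| Loss in total | Complete patients |
|---|---|
| 5% (assumed) | 43.7 |
| 10% (protocol) | 41.4 |
| 20% (assumed) | 36.8 |
| 30% (assumed) | 32.2 |

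At the protocol's figure, 4 to 5 randomised patients drop out of the analysis.

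**3. Precision at week 12.** If every lost patient attended week 12 and then missed week 24, an all-available analysis has 46 values at week 12 and default deletion leaves 41. The interval widens by √(46/41) = 1.059, about 6%. A patient lost before week 12 has no 12-week value under either method, so any earlier loss makes the difference smaller. At the protocol's rate, 6% is therefore an upper bound.

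**4. Direction of possible bias (illustration only).** Assume a true effect of −0.72 SD, a correlation of 0.5 between visits, poor 12-week responders in the intervention arm more likely to miss week 24, and random loss in controls.

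| Loss | Completers, week 12 | Completers, week 24 | All available data, likelihood |
|---|---|---|---|
| 10% | −0.84 | −0.78 | about −0.72 |
| 20% | −0.95 | −0.84 | about −0.72 |

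The likelihood estimate recovers the truth because loss here depends only on observed values. The scenario shows a mechanism by which deletion could exaggerate the effect. None of its settings comes from the documents.

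**The case against.** The strongest reply is that the article never mentions completers or exclusions and says the opposite: "The statistical analysis will be based on intention-to-treat analysis". Missing-data handling is commonly left to an analysis plan, and none is shown here. Imputing missing visits before the ANOVA, or fitting the model in long format with patient as a factor, would keep incomplete patients. All of that stands. A reader might infer that the trial will certainly report a completer analysis; the documents do not support this, because deletion is the default of the named method and not a stated rule. What remains is that the sentence names a model whose default runs against the principle beside it, so the point is about what is written and not only about missing detail.

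The fall from 46 to 41 is also not an unplanned loss of power, since the 10% allowance covers it. Nothing here shows that 46 is wrong.

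A reader might also infer a sizeable bias. Removing the worst 10% or 20% of one arm would move that arm's mean by 0.20 or 0.35 SD with no true effect, but this requires loss fully determined by outcome in one arm only. The documents describe nothing of the kind; the one reason they give for losses is the length of the procedures.

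Finally, the losses expected in the research design overview concern the follow-up evaluation. That is week 24 for the intervention arm but week 36, outside the model, for controls. For controls, only the general 10% allowance bears on the modelled visits.

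**Conclusion.** The point holds in a limited form. The named model, at its default, does not analyse all randomised patients, and so does not by itself deliver intention-to-treat. With the protocol's own 10% loss, about 41 of 46 patients would be analysed, and valid 12-week values of patients who miss week 24 would be discarded. The cost in 12-week precision is at most about 6%, reached only if all losses come after week 12. Bias is possible because week 24 is a different kind of visit in each arm, but that loss will differ by arm is an inference, and the size of any bias cannot be derived from the documents. The conclusion rests on the procedure being run in its standard form with no prior imputation, which the article neither states nor rules out. This is worth correcting before analysis. It does not call the sample size or the design into question.

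**What to change.** Replace the repeated-measures ANOVA with a likelihood-based linear mixed model for repeated measures, with arm, visit and arm-by-visit terms, using every available visit of every randomised patient in the assigned arm. Report the 12-week between-arm contrast from that model; the treatment-time interaction can still be tested in it. Multiple imputation of missing visits before the planned ANOVA is an acceptable alternative if the sponsor prefers to keep that method. The choice of covariance structure and degrees-of-freedom method can be left to the analysis plan.

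Cost: a change of analysis wording. N stays at 46, no further data are collected, and standard software suffices. The mixed model assumes that data are missing at random given the observed values, and the plan should say so.

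### Baseline is analysed as one level of the time factor; adjusting for it as a covariate would estimate the 12-week effect at least as precisely, from data already collected

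*Protocol article*

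**What the plan says.** The section on sample size and analysis fixes the model: "general linear models of analysis of variance for repeated measure will be used to detect treatment-time interactions". It also fixes the visits: "The outcome measures will be compared among baseline, 12 weeks, and 24 weeks". Baseline is therefore a level of the time factor, and no baseline covariate is named.

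The text under Figure 1 says of the control group: "They also are assessed at baseline condition (A1) and after 12 weeks (A2". Controls have usual care up to that second assessment and then receive the 12-week intervention.

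The same section on sample size gives the inputs one by one.

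- Effect size: "The sample size calculation was made using an effect size of 0.36 (moderate effect size), considering the primary outcome measure of peak plantar pressure".
- Number and power: "A sample size of 46 subjects is needed to provide 81% power to detect a moderate effect difference between the highest and lowest group pressure".
- Test: "assuming an alpha level of 0.05 and an statistical design of F test of repeated measures (between and within effects".
- Attrition: "assuming a 10% loss to follow-up".
- Variability: "We took the SD estimates from a study we completed, wherein we recruited a similar patient cohort [71", without a figure.

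It states no correlation between visits and no allocation ratio, and it does not say whether 0.36 is Cohen's f or d.

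**The concern.** When a baseline measured before treatment enters as a repeated outcome, the baseline-to-12-week part of the treatment-time interaction is the difference between arms in raw change. That subtracts the whole baseline value (slope 1), whereas the data support a slope of about rho. Two things follow.

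- **Precision.** The change score carries more variance than an estimate conditioned on baseline whenever rho is below 1.
- **Imbalance.** With about 20 completers per arm, the arms can easily differ at baseline by chance. Raw change over-corrects for such a difference by (1 − rho) times its size.

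This matters because the trial is small, only the 12-week contrast sets treated against untreated patients, and the baseline values are collected in both arms anyway.

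**Working it through.** **Inputs.** From the sample size section: 46 patients, 81% power, alpha 0.05, effect size 0.36, 10% loss. Completers: 46 × 0.9 = 41.4, taken as 41. Assumed, because not stated: 1:1 allocation; 0.36 is Cohen's f, so d = 2 × 0.36 = 0.72 SD at week 12; equal variances at both visits; rho from 0.3 to 0.8.

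**The plan's own figure.** For a three-visit, two-arm interaction with noncentrality f² × 2(N − 2) and 2 and 2(N − 2) degrees of freedom:

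- N = 41: 0.1296 × 78 = 10.11, power 80.4%.
- N = 42: 0.1296 × 80 = 10.37, power 81.5%.

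So 81% is reproduced to within rounding, and 41/0.9 rounds up to 46.

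**Variances for the 12-week effect** (per patient, in units of the outcome variance):

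- Change score: 2(1 − rho).
- Baseline-adjusted: 1 − rho².
- Ratio: (1 − rho²) / [2(1 − rho)] = (1 + rho)/2.

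The ratio is 0.65, 0.75, 0.85 and 0.90 at rho 0.3, 0.5, 0.7 and 0.8. It is below 1 for every rho below 1, so the direction does not depend on the assumed value.

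**Power with 41 completers.** The noncentrality is N d²/4 divided by the variance above, and N d²/4 = 41 × 0.5184/4 = 5.31. Degrees of freedom are 1 and 39 (change) or 1 and 38 (ANCOVA). At rho 0.5 the noncentralities are 5.31/1 = 5.31 and 5.31/0.75 = 7.08.

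| rho | change score | ANCOVA | gain (points) |
|---|---|---|---|
| 0.3 | 47.6% | 65.4% | 17.7 |
| 0.4 | 53.7% | 68.8% | 15.2 |
| 0.5 | 61.3% | 73.7% | 12.4 |
| 0.6 | 71.0% | 80.2% | 9.2 |
| 0.7 | 82.7% | 88.2% | 5.5 |
| 0.8 | 94.5% | 96.3% | 1.8 |

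With all 46 patients at rho 0.5: 66.6% against 78.7%, a gain of 12.1 points.

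**If 0.36 is d.** With 41 completers at rho 0.5, power is 20.3% against 25.4%. The gain is 6.0 points at rho 0.3, 5.2 at 0.5 and 3.8 at 0.8.

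**Against the three-visit, 2-df interaction.** With d = 0.72, 41 completers and the same group difference at 12 and 24 weeks, the gain is 16.1, 9.4 and 1.8 points at rho 0.3, 0.5 and 0.7, and about zero (−0.4) at 0.8.

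**If the change contrast itself had 81% power**, ANCOVA would add 13.0, 9.6, 5.8 and 3.8 points at rho 0.3, 0.5, 0.7 and 0.8.

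**Imbalance.** The standard error of the baseline difference is √(4/41) = 0.31 SD, so a difference beyond 0.3 SD in either direction arises in about one trial in three. At rho 0.5, raw change over-corrects a 0.3 SD difference by 0.5 × 0.3 = 0.15 SD.

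**The case against.** The strongest reply is that nothing here is wrong. The group-by-time interaction in a randomised trial is a valid test, and averaged over randomisations the change score is unbiased. A separate statistical analysis plan, not shown, may well add covariates. That stands: this is a choice between two valid analyses. The article does, however, fix baseline as a time level, so the point rests on what it states.

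A reader might infer that the planned analysis forfeits a definite amount of power. The documents do not support any single figure. The size depends on rho, on f against d and on the allocation ratio, none of which is given. It also depends on the comparator: the planned test covers three visits, and against it the gain is mostly smaller and vanishes at rho 0.8. That comparison assumes equal group differences at 12 and 24 weeks, which is doubtful because controls are treated in between.

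A reader might also set 61% beside the stated 81% and conclude that the sample size is wrong. That does not follow. The 81% is reproduced for a different test, by a formula that takes 0.36 as the effect size of the interaction itself and needs no correlation. The 61% translates 0.36 into a 12-week difference and assumes rho 0.5.

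Finally, a single baseline covariate does not fit the time-series pressure curves by which the main outcome is described, nor the manual muscle grades and the graded foot function tests. This limits the scope, but leaves peak pressure, contact area and the continuous secondary outcomes.

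**Conclusion.** The point holds as an improvement in efficiency, not as an error in the plan. For the 12-week effect, baseline adjustment has (1+rho)/2 of the change-score variance when the visit variances are equal, and it avoids over-correcting chance imbalance. The direction is certain for any rho below 1, apart from the one degree of freedom spent, which matters only as rho nears 1. The size is conditional: about 12 points of power at rho 0.5 and about 18 to 2 points over rho 0.3 to 0.8, given 41 completers, 1:1 allocation and 0.36 as Cohen's f; about 4 to 6 points if 0.36 is d.

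**What to change.** Before outcome data are seen, specify the 12-week between-group difference as the estimate of interest for peak pressure and contact area in each plantar area and for each continuous secondary outcome. Estimate it by ANCOVA, with the patient's own baseline value of the same variable (and the same plantar area, where that applies) as covariate, or by a mixed model with the baseline mean constrained equal between arms. Report the adjusted difference with its 95% confidence interval. The time-series curve analysis and the ordinal muscle and foot function scores are outside this change.

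The cost is analysis wording and one degree of freedom. No extra patients, visits or measurements are needed.
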